## Abstract

**Introduction:**

Hypertensive disorders of pregnancy (HDP), including gestational hypertension and pre-eclampsia, affect approximately 10% of pregnancies worldwide and contribute significantly to fetal and maternal morbidity and mortality. Early identification of HDP would facilitate targeted surveillance and personalised care in order to mitigate the severity of complications and improve pregnancy outcomes. Uric acid is a marker of oxidative stress, inflammation and endothelial dysfunction, and has been proposed as a predictor of hypertensive disease. Salurate is a salivary uric acid test that has the potential to identify pregnant women at risk of developing HDP several weeks before clinical manifestation.

**Methods and analysis:**

This is a prospective, multicentre, observational, cohort study with health economics evaluation. Women aged 16 and above, with a viable singleton pregnancy at <16 weeks gestation and a combined first trimester pre-eclampsia risk of >1:300 will be eligible for recruitment. Participants will perform weekly remote salivary uric acid testing from enrolment until the conclusion of pregnancy and upload results of colourimetric paper tests via a smartphone application. We will validate a predictive algorithm that analyses colour data from several consecutive samples to detect patterns that predict whether HDP is likely to occur. The primary outcome is test performance for the prediction of HDP. Secondary outcomes include adherence to sampling and test performance for predicting gestational diabetes, stillbirth and fetal growth restriction. Data on pregnancy outcomes will be collected from the medical notes, compared with the predictions made by the algorithm and subjected to statistical analysis.

**Ethics and dissemination:**

Approval has been obtained from Cambridge East Research Ethics Committee (REC reference 24/EE/0123), Medicines and Healthcare products Regulatory Agency (CI/2024/0038/GB) and Health Research Authority (IRAS ID 337290). Results of the study will be published in peer-reviewed journals and presented at national and international conferences.

**Trial registration number:**

ISRCTN17992452.

**Protocol version:**

4, 4 July 2024.

STRENGTHS AND LIMITATIONS OF THIS STUDYThis is a large, multicentre study which aims to include participants from a broad range of ethnicities and socioeconomic backgrounds.The secondary outcomes will allow us to assess if salivary uric acid could also be used as a predictor of related placentally mediated adverse pregnancy outcomes.The potential for inadequate assessment of specificity or sensitivity of salivary uric acid for hypertensive disorders of pregnancy is mitigated by employing a large sample size.Possible poor compliance with a weekly testing regime will be partly mitigated by reminders through a customised mobile application and opportunities to make up missed tests.

## Introduction

 Hypertensive disorders of pregnancy (HDP) affect approximately 10% of pregnancies worldwide and are among the leading causes of maternal and fetal morbidity and mortality, contributing to approximately 14% of maternal deaths every year.^1 2^ Early prediction and diagnosis would facilitate targeted surveillance, which would improve allocation of resources for healthcare providers and avoid unnecessary hospital attendance for patients. Traditional antenatal surveillance includes blood pressure and urinalysis at every visit, which identifies HDP at the time of manifestation.^3^ Recent advancements in first-trimester combined screening, such as with the Fetal Medicine Foundation (FMF) algorithm, have improved risk assessment for the development of pre-eclampsia, which facilitates effective preventative interventions such as daily aspirin from the first trimester.^4^ The introduction of soluble fms-like tyrosine kinase-1 and placental growth factor (PlGF) as diagnostic triage tools in symptomatic women has aided clinical decision making in admission and treatment of women with suspected HDP.^5^,^7^ There remains no effective tool that aids continuous and dynamic risk assessment of HDP throughout pregnancy in asymptomatic women, which would allow for a personalised care plan and improved mitigation of the severity of disease and complications.

Uric acid has been implicated in oxidative stress, inflammation and endothelial dysfunction and, therefore, proposed as a useful biomarker and treatment target in neurological, cardiovascular and metabolic conditions.^8^
^9^ In pregnancy, uric acid has been proposed as a pathogenic, diagnostic and predictive marker of hypertensive disease, with some studies suggesting salivary uric acid could be used as a surrogate, or even more accurate, marker in hypertensive diseases in pregnancy.^10 11^
12,14 Salivary biomarkers for disease detection and monitoring are a potential tool for a variety of conditions.^15^ Saliva sampling is simple, non-invasive and does not require clinical involvement, making it ideal for remote monitoring. Pilot studies have demonstrated that elevated salivary uric acid in pregnant women correlates with an increased risk of developing HDP.^13^

The Salurate system is a weekly salivary uric acid self-sampling test with the potential to provide predictive information before symptoms appear. It could fill a critical gap in current clinical approaches, allowing for proactive and timely management. If the study demonstrates Salurate’s predictive capabilities are reliable and accurate, its implementation could lead to improved maternal and fetal health outcomes. Early detection of high-risk pregnancies may enable healthcare providers to initiate appropriate interventions promptly, reducing the incidence and severity of HDP, and ultimately leading to improved maternal and neonatal health. Salurate has the benefits of being convenient, simple, pain-free, home-use and non-invasive. As a remote monitoring tool, Salurate effectively minimises the burden of hospital visits for expectant mothers and fosters seamless communication between women and healthcare professionals.

The Salurate study will add to the expanding pool of evidence supporting the adoption of technology-driven healthcare solutions, especially in obstetrics. The findings from this study have the potential to influence clinical practice and public health policies. If Salurate proves to be effective in predicting HDP, it could be integrated into routine prenatal care protocols, enabling healthcare providers to offer more personalised and proactive care to pregnant women.

### Objectives

To assess the efficacy of the Salurate pregnancy remote self-monitoring system in predicting the onset of HDP. By comparing the Salurate system with traditional screening and diagnostic methods, this study aims to determine the sensitivity, specificity, positive predictive value (PPV) and negative predictive value (NPV) of Salurate in identifying pregnant women who will go on to develop HDP. Additionally, the study aims to evaluate the time-to-diagnosis using the Salurate system in comparison to conventional diagnostic approaches.

#### Primary objective

To test the hypothesis that the inclusion of the Salurate pregnancy remote self-monitoring system in pregnant women’s care pathway would help to predict the subsequent development of HDP prior to what is currently possible using traditional methods.

#### Secondary objectives

To assess whether Salurate could detect the occurrence of other placentally mediated adverse pregnancy outcomes such as fetal growth restriction (FGR), small for gestational age (SGA) birth, spontaneous preterm birth (sPTB), stillbirth and gestational diabetes mellitus (GDM).To assess the cost-effectiveness of Salurate testing compared with current care methods.To assess the degree of compliance of pregnant women to a self-sampling weekly Salurate test regimen.To assess the algorithm efficacy in a demographically diverse population.

### Salurate system

Salurate is a non-invasive, home-use self-sampling system. A saliva sample is applied to colourimetric test paper (encapsulated in a test cartridge). An enzymatic reaction occurs, which produces a purple colour of varying intensities. The intensity of the colour change is directly proportional to the salivary uric acid concentration. While the colour change on the test paper may be visible to the naked eye, accurately interpreting the results is not possible through visual observation alone. The Salurate prediction algorithm employs advanced image analysis techniques to evaluate images submitted over the past few weeks before generating a prediction (figure 1).

**Figure 1 F1:**
[figure not shown]
Relationship of colourimetric test to uric acid concentration.

Components (figure 2):

The swab: a prepackaged, sterile swab commonly used for saliva collection. Single use and manufactured from a non-hazardous polyurethane foam.Test cartridge: a bespoke enzymatic uricase colourimetric test assay. The intensity of the purple colour formed is directly proportional to the concentration of uric acid in the saliva sample. The test paper is encapsulated into a single-use test cartridge.Salurate box: Contains all the equipment required to take a sample. The top of the box includes a designated test cartridge area for the purpose of facilitating image capture. The box top is also labelled with the study identification (ID) in alphanumeric and QR code and includes a red/green/blue (RGB) colour chart. The colour chart is used to adjust for differing lighting conditions and adjust for a wide range of camera phone hardware.Mobile application (figure 3): ‘The Salurate app’ facilitates the photographing of colourimetric test paper (test cartridge), guides the participant through the sampling process, transmits the image to the Salurate Secure Server, reminds the participants when to take their sample and provides a source of information about the study.Salurate secure server: a cloud-based server system that utilises the AWS platform. Primary functions:To receive images transmitted from the Salurate app.To identify and extract colourimetric data from these images, and to generate predictions based on this extracted data.To act as a database of test kits, storing information including (but not limited to anonymised participant ID number, test kit batch information, inventory and location, and information relating to recruitment centres and recruiters.To control and issue notifications to participants and recruiters.Clinical portal: a means of viewing, updating and extracting data from the Salurate secure server. Primary functions:To facilitate the registering of test kits during the recruitment process.To facilitate data input on the case report form (CRF).To facilitate the control of inventory.To allow low and high-level administrative access to data.

**Figure 2 F2:**
[figure not shown]
Components of the salurate system.

**Figure 3 F3:**
[figure not shown]
Salurate mobile application.

Using the Salurate system:

Participants will be sent a reminder through the Salurate mobile application on a weekly basis to take a saliva swab and upload a photo of the result.

Steps of obtaining a sample (figure 4):

Prepare one test cartridge and one swab, open the Salurate app and select ‘TAKE SAMPLE’.Place the swab under the tongue and leave it there for 30 s.Press the swab into the testing area of the test cartridge and hold it there for 3 s.Let the cartridge sit for 5 min.Place the test cartridge on top of the Salurate box in a well-lit area and take a picture of the testing area, ensuring the colour chart and Study ID number are visible in the photo.Submit the photo to the server using the Salurate mobile application.

**Figure 4 F4:**
[figure not shown]
Steps of obtaining a saliva sample.

## Methods

We used the Standard Protocol Items: Recommendations for Interventional Trials checklist when writing our report.^16^

### Recruitment and sampling

This is a prospective, multicentre, observational cohort study spanning two trusts across three sites in south-west London: St George’s Hospital NHS Foundation Trust, Epsom and St Helier University Hospitals NHS Trust. The study schema is shown in figure 5. Women attending their first trimester nuchal scan will have a calculation of their risk of hypertensive disease in pregnancy as per the first trimester combined pre-eclampsia screening algorithm.^17^ If their risk of preterm pre-eclampsia is calculated as greater than 1:300 and they satisfy the remaining inclusion criteria, they will be approached and recruited to undertake weekly remote salivary uric acid testing using the Salurate system until the conclusion of pregnancy, with written consent obtained. Participation involves no additional appointments or travel but could extend the initial clinic visit by up to 30 min. Data on antenatal and perinatal maternal and neonatal outcomes will be collected, and the relationship of test results to outcomes will be analysed by a medical statistician. The study is expected to open in September 2024, will be open to recruitment until December 2025 and will close in June 2026.

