### Inclusion and exclusion criteria

All women aged 16 years old and over with a viable singleton intrauterine pregnancy between 10 and 16 weeks’ gestation at the time of enrolment, a risk of preterm pre-eclampsia of >1:300 as determined by the Aspirin for Evidence-Based Pre-eclampsia Prevention algorithm^5^ and able to provide informed consent will be eligible for recruitment. The algorithm combines maternal factors, mean arterial pressure (MAP), uterine artery pulsatility index (UtA-PI) and maternal serum pregnancy-associated plasma protein-A (PAPP-A) and PlGF at 11–13 weeks’ gestation and is used routinely at recruiting centres. Exclusion criteria: significant comorbidities that will interfere with participation or physical incapacitation from performing self-sampling; presence of serious mental illness, learning disabilities or educational status or language barrier that influences capacity to use the Salurate app or understand the instructions for use; lack of access to a smartphone or internet at home; periodontal disease, gingivitis or oral cancer.

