### Schedule of events

Participants will be approached at their initial visit, and subject to eligibility and consent, will be enrolled in the study. They will be issued a Salurate sampling kit, and a member of the research team will guide the participant through the process of taking a sample and using the Salurate app to upload a picture of their test. Their unique study ID will be registered on the Salurate Clinician Portal and an initial CRF will be completed, recording data on maternal demographics, medical history, obstetric history and data from their first trimester combined pre-eclampsia screening (MAP, PAPP-A, crown-rump length, left and right UtA-PI and risk of preterm pre-eclampsia).

Each participant will submit weekly samples from enrolment until the conclusion of pregnancy. A predictive model algorithm analyses the data supplied by the participants via the Salurate app and provides a prediction with the likelihood of an adverse event (hypertensive disease of pregnancy, FGR) occurring. Several colourimetric measurements are extracted from the uploaded test from the participants, which relate to the concentration of uric acid in the saliva sample. The algorithm looks at the change from week to week, and using the trend from preceding weeks calculates a risk of HDP within a given timeframe. The trend is based on specific patterns of uric acid levels linked with known HDP events learnt from previous trials data. This prediction is calculated post hoc and not revealed to the participant or clinical trial research team. Data on the primary and secondary outcomes will be retrieved from the participants’ medical notes at the conclusion of pregnancy and added to the CRF.

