### Data analysis

The quantitative data for this study will be analysed and reported according to the relevant reporting guidelines.^16 21^ All analyses will be performed in StataSE V.16.1 statistical analysis software. All clinical primary and secondary outcomes (maternal and neonatal) will be presented across the whole cohort as percentages with 95% CIs. Missing outcomes data will be presented. Women’s characteristics at enrolment into the study will also be presented with percentages or summary statistics as appropriate.

Salivary uric acid concentration (Salurate) observations will be presented graphically over time from the initial 10–14 weeks pregnancy record through to the end of study participation (1) for the whole cohort, (2) by primary outcome (HDP present or absent) and (3) for each secondary outcome, including adverse maternal or perinatal outcomes. Numbers and percentages of missing Salurate reports will be presented by week of pregnancy with the number of women participating in the study as the denominator (which may vary in the last weeks of the study depending on when they give birth). This will be used to assess the degree of compliance of women to the testing regimen. No multiple imputation or other forms of missing data replacement will be used to estimate missing values of Salurate. No missing data replacement will be employed for clinical outcomes or participant’s characteristics at enrolment, and every effort will be made to record these data. We anticipate that rates of data missingness will be low.

A mixed-methods analysis of longitudinal data will be used to determine the relationship between Salurate results and the primary and secondary outcomes in this cohort. The Salurate algorithm will be employed, and its sensitivity, specificity, PPV and NPV to identify the primary outcome will be presented with 95% CIs. We will also determine how soon the primary outcome would be indicated using Salurate results and compare this with traditional prediction methods such as the FMF algorithm or National Institute for Health and Care Excellence (NICE) checklist. Subgroup analyses will explore whether the Salurate algorithm has greater diagnostic value in particular women according to baseline characteristics, although these analyses may not have enough statistical power to be definitive.

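### The stated dates leave about 26 weeks between last recruitment and study close, too short for late recruits to be followed to the end of pregnancy on most readings

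*Protocol article*

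**What the plan says.** The calendar is in the Protocol article, Recruitment and sampling: "The study is expected to open in September 2024, will be open to recruitment until December 2025 and will close in June 2026". It gives months without days.

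Eligibility (Inclusion and exclusion criteria) is a "viable singleton intrauterine pregnancy between 10 and 16 weeks’ gestation at the time of enrolment". The qualifying risk score uses measurements taken "at 11–13 weeks’ gestation and is used routinely at recruiting centres", and Recruitment and sampling places the approach to women at the nuchal scan. Data analysis describes the uric acid series as running "from the initial 10–14 weeks pregnancy record through to the end of study participation".

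Follow-up is set per woman in Schedule of events: "Each participant will submit weekly samples from enrolment until the conclusion of pregnancy". Primary and secondary outcome data "will be retrieved from the participants’ medical notes at the conclusion of pregnancy and added to the CRF". The primary outcome (Outcomes) is HDP of any onset, with no restriction to preterm disease. Data analysis rules out replacing missing clinical outcomes and expects little missingness.

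**The concern.** Two statements have to fit together: a fixed closing month, and follow-up of every woman to the end of her pregnancy. If the interval after the last enrolment is shorter than the rest of a pregnancy, some late recruits will still be pregnant at close.

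What is at stake is selection rather than numbers. Among late recruits, those who deliver early, including any delivered because of HDP, would have complete records, while those with longer pregnancies would not. Weeks 37 to 42 are part of the period at risk for the primary outcome. An undelivered woman without HDP at close therefore has an unresolved status, and treating it as resolved would affect sensitivity, specificity and both predictive values. Her last weekly samples would be missing too.

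**Working it through.** **Inputs from the article:** recruitment September 2024 to December 2025; close June 2026; usual entry around 11–13 weeks (10–16 allowed); N = 4000; 11.5% prevalence of any event of interest.

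**Assumptions, not in the article:** even accrual from 1 September 2024; delivery at 40 weeks with 42 as the upper end (step 2), or a normal distribution with mean 39.0–39.5 and SD 1.8 weeks (step 4); in step 4, entry uniform over 11–14 weeks.

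**1. The plan's own figure.** Events = 4000 × 0.115 = 460. Half-width = 1.96 × √(s(1−s)/460), which is 4.57% at s = 0.5 and 2.74% at s = 0.9. This agrees with the stated ±5% and ±3%. The calendar has no derivation to reproduce.

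**2. Time needed against time available.** From entry at 13, 12 and 11 weeks, 40 weeks is 27, 28 and 29 weeks away, and 42 weeks is 29, 30 and 31 weeks away. Time available:

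| Last enrolment | Close | Days | Weeks |
|---|---|---|---|
| 31 Dec 2025 | 30 Jun 2026 | 181 | 25.9 |
| 1 Dec 2025 | 1 Jun 2026 | 182 | 26.0 |
| 31 Dec 2025 | 1 Jun 2026 | 152 | 21.7 |
| 30 Nov 2025 | 30 Jun 2026 | 212 | 30.3 |

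Gestation at close = gestation at entry + weeks available. For 31 December to 30 June, women entering at 11, 12 and 13 weeks are at 36w6d, 37w6d and 38w6d. They reach 40 weeks on 22, 15 and 8 July, and 42 weeks on 5 August, 29 July and 22 July.

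**3. Hand check of the share affected.** For recruitment through 31 December (486 days), women below 40 weeks at close = 4000 × (days from the last safe entry date to 31 December) / 486.
- Close 30 June, entry at 12 weeks: last safe date 16 December, 15 days, 123 women (3.1%). Entry at 13 weeks: 23 December, 8 days, 66 women (1.6%).
- Close 1 June, entry at 12 weeks: 17 November, 44 days, 362 women (9.1%). Entry at 13 weeks: 24 November, 37 days, 305 women (7.6%).

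**4. With a spread of delivery dates.** By simulation, a woman is undelivered if entry date + (gestation at delivery − gestation at entry) falls after close. The ranges cover mean delivery at 39.0 to 39.5 weeks.

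| Recruitment ends | Close 1 Jun | Close 15 Jun | Close 30 Jun |
|---|---|---|---|
| 30 Nov | 61–80 | 14–22 | 1–3 |
| 31 Dec | 276–305 | 163–191 | 67–86 |

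As a share of 4000, 67–86 is about 2% and 276–305 is about 7–8%. Independent runs differ by a few women.

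**5. Effect on precision.** Removing 310 women leaves 3690 × 0.115 = 424 events, with a half-width of 4.76% at s = 0.5 and 2.85% at s = 0.9. Both stay within the stated limits.

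**The case against.** The strongest reply is that the calendar is indicative. It gives months only and describes the opening as expected. Recruitment until December can mean that it stops as December begins. With a close at the end of June, that leaves about 30 weeks and almost nobody undelivered. This stands, and it is why the size has to be a range. It does need the earliest reading of one month and the latest of the other, and it leaves almost no time for notes retrieval.

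Second, the article does not say that follow-up stops at close, and the rule for each woman is explicit. An end-of-study definition may well be in the full protocol. This also stands. A reader might infer that term outcomes and final samples will be cut off; the article does not establish that. It states a date and a follow-up rule that do not fit together on most readings, and mentions no follow-up after June 2026.

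Third, nothing in the article says that undelivered women would be dropped or coded as HDP-absent. Those are possible consequences, not planned analyses.

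Fourth, the eligibility wording ("pregnancy between 10 and 16 weeks’ gestation at the time of enrolment") allows a 10-week entrant, who would reach 42 weeks only on 12 August 2026. That case is atypical, because the qualifying screen is at 11–13 weeks, and it should not set the size of the gap.

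**Conclusion.** The point holds as an inconsistency between the calendar and the follow-up rule. About 26 weeks are available on a same-day or end-of-month reading, against 27–29 weeks needed to reach 40 weeks from the usual entry point. The number undelivered at close runs from almost none to about 310 of 4000 (8%), with about 70–90 (2%) for 31 December to 30 June. These counts rest on the assumed accrual, entry and delivery distributions and on which days of the stated months are meant.

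A reader might infer that the sample size fails; it does not. The effect on the accuracy estimates is probably small for a close at the end of June. If 5–10% of 67–86 undelivered women later developed HDP (an assumption), that is about 3–9 women (0.05 × 67 to 0.10 × 86). The loss would still be selective for late disease and hard to repair after close. Severity is moderate to minor.

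**What to change.** Choose one of two changes and state it.

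1. Define study close as the last participant's conclusion of pregnancy plus a stated period for notes retrieval. For recruitment through 31 December 2025, women entering at 11–13 weeks reach 42 weeks by about 5 August 2026, and retrieval follows that. The cost is a date amendment and a few more weeks of follow-up.

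2. If June 2026 is fixed, end recruitment early enough for the last entrant to deliver. For a 30 June close, an 11-week entrant must enrol by 25 November 2025 to reach 42 weeks, so mid-November leaves a short margin for retrieval. A 1 June close would need about 27 October. Stopping in mid-November costs about six weeks of accrual, or roughly 380 women at an even rate if not made up (4000 × 46/486 = 379). That would leave about 416 events (3621 × 0.115) and a half-width of 4.8% at 50% sensitivity.

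In either case, give the last enrolment and close as dates, say whether close ends follow-up or the whole study, and state that no woman is classed HDP-absent before her pregnancy has concluded. This last rule makes explicit what Schedule of events already implies, and costs nothing.
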